Participants are invited to participate by the trial coordinator, who contacts the young person (and their parent or legal guardian for those under 18 years) to introduce the study and to offer an appointment to obtain written consent. After the trial coordinator obtains written consent, a research assistant or the trial coordinator conducts the baseline assessment. All participants receive assertive case management, crisis care and general psychiatric care during the pre-screening and assessment phase. Once eligibility for the trial is confirmed, the trial coordinator randomly and consecutively assigns participants to one of the three interventions in a ratio of 1:1:1 using a password-protected computer program with a randomisation sequence that was computer-generated by an independent statistician. Treatment allocation uses randomised permuted blocking, and participants are stratified by age (cut point of age 18 years), sex and the Centre for Epidemiological Studies Depression Scale Revised (CESD-R) [35] score (cut point = 37, which is the mean score for borderline personality disorder patients on entry to HYPE), thus minimising these potentially confounding factors. Following randomisation to a treatment group, the trial coordinator then randomly assigns participants to the next available trial clinician using a separate randomisation sequence that was also computer-generated by an independent statistician. The trial coordinator contacts the participant and the treating service to inform them of the treatment group and clinician allocation. The clinician then contacts the participant to arrange the first appointment. Thus, the trial coordinator conducts the consent and randomisation procedures separately from the blinded research assistants, using independently derived, password-protected, computer-generated randomisation sequences.

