### Treatment integrity

All treatment sessions are audio-recorded to enable treatment integrity checks. CAT and befriending are both manualised treatments. Integrity (adherence, competency and separation) will be managed via regular expert supervision for CAT and befriending. Each CAT therapist will have two randomly selected CAT session recordings rated for adherence and competency, using a scale designed specifically for CAT [38]. A random selection of 50 % of befriending clinicians will have two randomly selected sessions rated for adherence and competency, using a scale designed specifically for befriending [37], and for treatment separation using the CAT scale. The befriending scale measures whether the therapist: (i) redirects from unresolved conflicts to a neutral topic, (ii) redirects from discussion about symptoms to a neutral topic, (iii) chooses the most neutral line of questioning, (iv) reacts minimally to loaded speech (for example, symptoms, conflicts), (v) redirects from identity issues to a neutral topic and (vi) predominantly engages the client in neutral conversations on day-to-day subjects.

The HYPE service model is manualised, but YMHS is not. Integrity of HYPE and YMHS will be maintained through the structure of the services and clinician supervision. HYPE also uses checklists of the tasks of care. Measures have been implemented to reduce ‘contamination’ of treatments and thereby to ensure treatment separation. HYPE and YMHS are governed and administered by separate organisations. YMHS clinicians have never worked in HYPE and do not have regular clinical contact with HYPE staff. Clinicians conducting the befriending have no training in CAT and are excluded from conducting further befriending if they commence CAT training at any time during the trial. CAT practitioners are permitted to have exposure to other clinical intervention techniques.

A random selection of 50 % of case managers will have two randomly selected sessions rated for treatment separation (to ensure that CAT is not being done covertly), using the above-mentioned CAT scale [38].

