### Statistical analyses and sample size determination

To determine whether there are group differences on the primary and secondary outcome measures at 12 months, a series of mixed effects model repeated measures analysis of variances models (MMRM) will be employed. The within groups factor will be time, and the group will serve as the between subjects factor. MMRM is a preferred method for analysing clinical trial data in psychiatry in comparison with the more traditional repeated measures analysis of variance and analysis of covariance models [55]. MMRM is advantageous because it includes all existing data in the model, there is no imputation or substitution of missing data, dispersion and correlation can occur at all time points, and sensitivity analysis can be successfully conducted. Within these models, planned comparisons will be used to determine whether HYPE + CAT is superior to the other two interventions, and whether the HYPE service model leads to better outcomes compared with YMHS.

Power and sample size calculations have been based on a one-way analysis of covariance model with baseline values as the covariate, and the outcome measures as the dependent variables. It is assumed that the baseline covariate will account for 50 % of the variance in an outcome measure. Based on our published data [29, 56], we expect to find medium treatment effects on the primary outcome measures of interpersonal problems and social adjustment. Alpha has been set at 0.05 and power (1-β) for the study at 0.80. Given these parameters, we require 40 participants per group (120 in total) with at least two data points. Based upon the 14 % attrition rate in our previous randomised control trial we intend to recruit at least 45 cases per group.

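### The stated model and sample size ignore therapist clustering; if the therapist ICC is above zero, the SE of the HYPE + CAT versus befriending contrast is too small

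*Protocol article*

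**What the plan says.** The section on enrolment and randomisation describes two allocation steps. The participant is first randomised to an arm, and then "the trial coordinator then randomly assigns participants to the next available trial clinician using a separate randomisation sequence". The Interventions section makes the psychotherapy individual: up to 16 sessions of CAT or befriending.

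The Treatment integrity section handles therapists as units in their own right: "Each CAT therapist will have two randomly selected CAT session recordings rated for adherence and competency", and half of the befriending clinicians are sampled for rating. It also keeps the two roles apart. Befrienders have no CAT training and stop befriending if they begin it. HYPE and YMHS belong to separate organisations, and YMHS clinicians have never worked in HYPE.

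On the analysis, the statistical section states: "The within groups factor will be time, and the group will serve as the between subjects factor". On size: "Power and sample size calculations have been based on a one-way analysis of covariance model with baseline values as the covariate", with the assumption that "the baseline covariate will account for 50 % of the variance in an outcome measure". The expected effect is described only in words: "we expect to find medium treatment effects on the primary outcome measures of interpersonal problems and social adjustment". Finally, "Alpha has been set at 0.05 and power (1-β) for the study at 0.80". From these parameters the article derives 40 participants per group. No therapist term, ICC or design effect appears anywhere in it.

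**The concern.** Participants treated by the same therapist tend to have correlated outcomes. The MMRM's covariance structure covers correlation over time within a participant, but not correlation between participants of one therapist. Randomising participants to therapists makes caseloads comparable but does not remove that correlation.

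The problem falls on the contrast that the trial exists to estimate. Because CAT therapists and befrienders are different people, therapist is nested within type of psychotherapy. With few therapists, one or two unusually good or poor ones can look like an effect of CAT. The Discussion links the answer to whether services need practitioners with the two-year CAT training, so a falsely precise result here would have consequences.

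**Working it through.** **Inputs from the article:** three arms at 1:1:1; alpha 0.05; power 0.80; baseline R² = 0.50; 40 per group analysed; 45 per group recruited; 14% attrition.

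**Assumptions, because the article gives no figure:** medium effect d = 0.5; therapist ICC (of the baseline-adjusted outcome) 0.02, 0.05 or 0.10; 5, 8 or 10 participants per therapist (8, 5 or 4 therapists per arm).

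**1. The stated sample size.** Take d = 0.5 between the extreme arms with the third midway. Then f² = (0.25² + 0 + 0.25²)/3 = 0.0417 and f = 0.204. For the three-group ANCOVA F test, λ = 3n·f²/(1 − R²) = 120 × 0.0417/0.50 = 10.0 on 2 and 116 df. Power is 0.805 at n = 40 and 0.794 at n = 39. The stated 40 is reproduced with no design effect.

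**2. Therapists nested in every arm.** The design effect is DE = 1 + (m − 1)·ICC. The true SE is √DE times the naive SE. The actual size of a nominal 5% test is 2[1 − Φ(1.96/√DE)]. Example with m = 10 and ICC = 0.05: DE = 1 + 9 × 0.05 = 1.45; √1.45 = 1.204; size = 2[1 − Φ(1.628)] = 0.104. The power columns use 40 per arm and the correct SE.

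| m | ICC | DE | SE ratio | Type I error | Power, 3-group F test | Power, pairwise d = 0.5 | Power, CAT vs mean of both BEF arms, d = 0.5 | n per arm (40 × DE) |
|---|---|---|---|---|---|---|---|---|
| any | 0 | 1.00 | 1.00 | 0.050 | 0.80 | 0.88 | 0.95 | 40 |
| 5 | 0.02 | 1.08 | 1.04 | 0.059 | 0.77 | 0.86 | 0.94 | 44 |
| 10 | 0.02 | 1.18 | 1.09 | 0.071 | 0.73 | 0.82 | 0.92 | 48 |
| 5 | 0.05 | 1.20 | 1.10 | 0.074 | 0.72 | 0.82 | 0.91 | 48 |
| 8 | 0.05 | 1.35 | 1.16 | 0.092 | 0.67 | 0.77 | 0.88 | 54 |
| 10 | 0.05 | 1.45 | 1.20 | 0.104 | 0.64 | 0.74 | 0.85 | 58 |
| 8 | 0.10 | 1.70 | 1.30 | 0.133 | 0.56 | 0.67 | 0.79 | 68 |

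Simulation (20,000 runs per scenario) agrees: at ICC 0.05 the HYPE + CAT contrast runs at 0.075, 0.090 and 0.104 with 8, 5 and 4 therapists per arm.

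**3. The same befrienders serve both BEF arms.** The article leaves this open. Take 5 CAT therapists, 5 shared befrienders, ICC 0.05 and unit variance.

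- HYPE + CAT versus the mean of both BEF arms: true variance = (0.05/5 + 0.95/40) + (0.05/5 + 0.95/80) = 0.0556; naive variance = 1/40 + 1/80 = 0.0375. The ratio is 1.48. Simulated type I error is 0.104.
- Pooled HYPE versus YMHS: true variance = 0.5 × 0.05/5 + 1.5 × 0.95/40 = 0.0406; naive variance = 1.5/40 = 0.0375. The ratio is 1.08. Simulated type I error is 0.059.
- HYPE + BEF versus YMHS + BEF: befriender effects cancel. True variance = 2 × 0.95/40 = 0.0475; naive variance = 2/40 = 0.05. The ratio is 0.95. Simulated type I error is 0.047.

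**4. Slack in recruitment.** 45 × 0.86 = 38.7 analysed per arm, so no spare sample absorbs a design effect.

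**The case against.** The strongest reply is that a short statistical section in an article names the main factors and leaves random effects to an analysis plan that is not shown. This stands in part. The article does not say that time and group are the only terms, and one should not infer a deliberate decision to treat participants as independent. However, the article does list the parameters behind the 40 per group, and clustering is not among them. A later plan could repair the standard errors but not the sample size, with 135 already enrolled. Other readings of a medium effect need fewer than 40 (27 per group for f = 0.25, about 33 for a pairwise d = 0.5), which would leave some room. The article claims no such allowance.

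Secondly, the size is not anchored. No ICC, therapist count or caseload is given, and the term trial clinician is not tied to therapist or case manager. With 3 participants per therapist and ICC 0.02 to 0.05, DE is only 1.04 to 1.10 and the type I error 5.5% to 6.2%. This stands, and the conclusion must be conditional.

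Thirdly, a reader might infer that every arm contrast has too small an SE. The article does not support that: with shared befrienders, the comparison of the two BEF arms is not inflated, and pooled HYPE versus YMHS only slightly. Separately staffed services could still induce clustering there, but the article gives nothing to quantify it.

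Fourthly, the power loss depends on the test. If HYPE + CAT is compared with both BEF arms in one pooled contrast at d = 0.5, power stays near or above 0.80 throughout the table. This also stands; the type I error is the firmer part of the point.

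**Conclusion.** The point holds in conditional form. Analysed as the article describes, HYPE + CAT versus befriending has an understated SE and a type I error above 5% whenever the therapist ICC is positive and therapists treat more than one participant. Under an assumed ICC of 0.02 to 0.05 and 5 to 10 participants per therapist, with therapists nested in arms, the error rate is about 6% to 10%. It is somewhat higher if befrienders are shared and so carry double caseloads. At ICC zero nothing changes.

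The 80% power at 40 per group assumes no clustering. On the F test that reproduces the 40, power would be 0.64 to 0.77 under the same assumptions. For single contrasts at d = 0.5 it would be 0.74 to 0.86 (pairwise) or 0.85 to 0.94 (pooled).

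A reader might go further and conclude that the standard errors are certainly too small, or that all service contrasts are biased towards significance. The article supports neither.

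**What to change.** Add a random intercept for the treating therapist to the model that yields the 12-month contrasts. Define the unit (CAT therapist or befriender) and say whether befrienders work in both BEF arms. If they do, cross the therapist effect with arm. Use one common therapist variance unless arm-specific variances can be estimated, and Kenward-Roger or Satterthwaite degrees of freedom. Report the number of therapists, their caseloads and the estimated ICC.

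State that the 80% power at 40 per group assumes no therapist clustering, and show power over a range of ICCs. With enrolment at 135 this cannot change the design, but it tells readers how to weigh a null result.

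The clinician allocation comes from its own randomisation sequence, so no new data collection should be needed. The cost is a change of wording, somewhat wider intervals if the ICC is positive, and, if therapists are few, a variance estimate that may be zero or unstable. The plan should say in advance what is done in that case.

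If an analysis plan with a therapist term already exists, only the power statement needs correcting.

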### Interventions

The HYPE + CAT group receives up to 16 × 50 minute CAT sessions. Both the HYPE + BEF and YMH + BEF groups receive up to 16 × 50 minute sessions of befriending. Clinicians aim to deliver the 16 CAT or befriending sessions weekly, but the disorganised behaviour evident in many in this patient population means that it usually takes approximately 26 weeks to deliver them. Completion of 16 sessions marks the completion of all trial treatment. At the end of treatment or at any stage thereafter, participants can be referred for or seek additional treatment.

All participants receive case management and general psychiatric care as needed, and crisis and inpatient services accessed from the state mental health system, where indicated.

#### HYPE

The HYPE service model uses CAT as its theoretical model and common language. However, HYPE can be used with or without CAT as an individual psychotherapy. Key HYPE components include: (i) an explicitly collaborative approach with patients; (ii) assertive, ‘psychologically informed’ case management; (iii) flexible timing and location of sessions, including capacity for ‘outreach’ care in the community; (iv) active engagement and inclusion of families and carers; (v) use of a consistent, common and ‘plain language’ model across all aspects of care; (vi) psychoeducation for patients, families, carers, schools and others involved with the young person; (vii) integration of general psychiatric care within the same team, with specific assessment and treatment of co-occurring psychiatric syndromes (‘comorbidity’); (viii) access to after hours crisis and brief, goal-directed inpatient care; (ix) a focus on psychosocial recovery; (x) individual and group supervision of staff; (xi) maintenance of treatment fidelity. The rationale for this model has been formalised and published [24].

#### YMHS

Headspace provides high-quality, general mental health care delivered by specialist youth mental health clinicians within a multidisciplinary group practice setting. Clinicians diagnose mental disorders, develop a management plan, offer psychoeducation, conduct case management and offer general psychiatric care. General practitioner and/or psychiatric referrals and pharmacotherapy are initiated as indicated. Crisis and inpatient services are accessed from the state-based mental health system, as needed.

#### CAT

CAT is a time-limited, integrative psychotherapy that arose from a theoretical and practical integration of elements of psychoanalytic object relations theory and cognitive psychology, subsequently developing into an integrated model of development and psychopathology [23, 36]. CAT is practical and collaborative in style, with a particular focus upon understanding the individual’s problematic self-management and interpersonal relationship patterns and the thoughts, feelings and behavioural responses that result from these patterns. A central feature in CAT is the joint (patient–therapist) creation of a shared understanding of the patient’s difficulties and their developmental origins, using plain-language written and diagrammatic ‘reformulations’. These form the basis for understanding self-management and relationship problems both within and outside therapy, assist the patient in recognising and revising their dysfunctional relationship patterns and assist the therapist in avoiding or recovering from collusion with such relationship patterns.

CAT has particular theoretical advantages for early intervention for borderline personality disorder, especially because its integrative and ‘transdiagnostic’ approach encompasses the myriad co-occurring problems, which are the norm in this patient group, within the overall treatment model.

#### Befriending

Befriending is a manualised treatment that has been used in a wide range of psychotherapy trials [37] in order to control for many of the ‘common factors’ of psychotherapy, such as time in therapy, participant expectations and positive experiences of therapy. Befriending sessions are up to one hour in duration and are conducted weekly by a provisionally registered psychologist, in the same manner as a therapist would see a patient weekly. Each befriending session has the same format and consists of talking about neutral topics that interest the participant, such as vocational and educational activities, music, sport, books, cooking and pets. If the participant finds verbal interaction difficult, activities such as board games, walking or playing sports can be used with a view to using the activity as a tool to engage the participant in further neutral conversation during and after the activity. The therapist’s primary goals are to keep the participant engaged for the full duration of therapy and to keep the conversation or activity as close to a neutral ‘pleasant chat’ as possible. When emotionally loaded topics arise, such as symptoms or interpersonal problems, the therapist gently redirects the participant to more neutral topics.

Befrienders are trained and supervised by one of the investigators (JG) and another clinical psychologist, both of whom are expert in the intervention.

### Treatment integrity

All treatment sessions are audio-recorded to enable treatment integrity checks. CAT and befriending are both manualised treatments. Integrity (adherence, competency and separation) will be managed via regular expert supervision for CAT and befriending. Each CAT therapist will have two randomly selected CAT session recordings rated for adherence and competency, using a scale designed specifically for CAT [38]. A random selection of 50 % of befriending clinicians will have two randomly selected sessions rated for adherence and competency, using a scale designed specifically for befriending [37], and for treatment separation using the CAT scale. The befriending scale measures whether the therapist: (i) redirects from unresolved conflicts to a neutral topic, (ii) redirects from discussion about symptoms to a neutral topic, (iii) chooses the most neutral line of questioning, (iv) reacts minimally to loaded speech (for example, symptoms, conflicts), (v) redirects from identity issues to a neutral topic and (vi) predominantly engages the client in neutral conversations on day-to-day subjects.

The HYPE service model is manualised, but YMHS is not. Integrity of HYPE and YMHS will be maintained through the structure of the services and clinician supervision. HYPE also uses checklists of the tasks of care. Measures have been implemented to reduce ‘contamination’ of treatments and thereby to ensure treatment separation. HYPE and YMHS are governed and administered by separate organisations. YMHS clinicians have never worked in HYPE and do not have regular clinical contact with HYPE staff. Clinicians conducting the befriending have no training in CAT and are excluded from conducting further befriending if they commence CAT training at any time during the trial. CAT practitioners are permitted to have exposure to other clinical intervention techniques.

A random selection of 50 % of case managers will have two randomly selected sessions rated for treatment separation (to ensure that CAT is not being done covertly), using the above-mentioned CAT scale [38].

### Outcome measures

The primary endpoint of the trial is 12 months after baseline assessment. Assessments occur at 3, 6, 12 and 18 months after baseline. Table 1 lists the primary and secondary outcomes, along with subsidiary measures. Multiple methods are being employed to assess outcomes. These include independent observer rating, self-report, and Mobiletype© [39], a novel method of *in vivo* ecological momentary assessment.

**Table 1 Tab1:** Schedule of outcome measures

	Time point (months)				
Measure	Baseline	3	6	12	18
Primary outcomes					
Inventory of Interpersonal Problems Circumplex Version (IIP-C)	✓	✓	✓	✓	✓
Social Adjustment Scale Self-Report (SAS-SR)	✓	✓	✓	✓	✓
Secondary outcomes					
Client Satisfaction Questionnaire (CSQ-8)	✓	✓	✓	✓	✓
Borderline Personality Disorder Severity Index (BPDSI-IV)	✓	✓	✓	✓	✓
Ecological momentary assessment of suicidal ideation and deliberate self-harm^a^	✓	✓	✓	✓	✓
Ecological momentary assessment of Positive and Negative Affect Scale (PANAS)^a^	✓	✓	✓	✓	✓
Beck Suicidal Ideation Scale (BSS)	✓	✓	✓	✓	✓
Suicide Attempt and Self-Injury Interview (SASII)	✓	✓	✓	✓	✓
Centre for Epidemiological Studies Depression Scale Revised (CESD-R)	✓	✓	✓	✓	✓
Montgomery–Aspberg Depression Rating Scale (MADRS/SIGMA)	✓	✓	✓	✓	✓
Alcohol Use Disorders Identification Test (AUDIT)	✓	✓	✓	✓	✓
Opiate Treatment Index (OTI - Section II)	✓	✓	✓	✓	✓
Subsidiary measures					
Difficulties in Emotional Regulation Scale (DERS)	✓	✓	✓	✓	✓
Quality of Life (AQoL-8D)	✓	✓	✓	✓	✓
Social and occupational functioning (SOFAS)	✓	✓	✓	✓	✓
Working Alliance Inventory (WAI)^b^	^b^	^b^	^b^		
Demographics	✓	✓	✓	✓	✓
Treatment information	✓	✓	✓	✓	✓
Diagnosis DSM-IV SCID-I/P	✓	✓	✓	✓	✓
Diagnosis DSM-IV SCID-II	✓			✓	✓

^a^Ecological momentary assessment uses the Mobiletype© mobile phone system to capture suicidal ideation, deliberate self-harm and affective state *in vivo*. Assessments occur six times per day for six days

^b^Administered at the commencement of treatment, mid-treatment and post final treatment session

The primary outcome is adaptive functioning, defined by measures of interpersonal problems [40] and social adjustment [41]. This was chosen in light of the evidence that impairments in adaptive functioning among individuals with borderline personality disorder tend to be persistent and refractory to current treatments [14]. The Inventory of Interpersonal Problems Circumplex Scales (IIP-C) [40] has 64 self-report items, rated using a five-point scale ranging from 0 (not at all) to 4 (extremely). It contains eight scales (Domineering, Vindictive, Cold, Socially Inhibited, Overly Accommodating, Non-assertive, Self-Sacrificing, Intrusive). The Social Adjustment Scale Self-Report (SAS-SR) [41] has 54 self-report items, scored on a five-point scale, measuring instrumental and expressive role performance over the previous 2 weeks. It yields scores in six domains (Primary Relationship, Work, Social and Leisure, Extended Family, Parental (own children) and Family Unit (partner or children)) and a total score, calculated by averaging all applicable items. The SAS-SR contains ‘skip-outs’, so that non-applicable items are omitted, making it appropriate for the age range of participants in the proposed study.

Secondary outcomes measure client satisfaction [42], borderline personality disorder features [43], suicidal ideation and deliberate self-harm [39, 44, 45], affective instability [39, 46], depression [35, 47] and substance use [48, 49]. Subsidiary outcome measures include emotion regulation [50], quality of life [51], a summary measure of social and occupational functioning [52], therapeutic alliance [53] and demographic, treatment and diagnostic information [32, 54].

